## Abstract

**Introduction:**

Emergency department (ED) visits for epilepsy are common, costly, often clinically unnecessary and typically lead to little benefit for epilepsy management. An ‘Alternative Care Pathway’ (ACP) for epilepsy, which diverts people with epilepsy (PWE) away from ED when ‘999’ is called and leads to care elsewhere, might generate savings and facilitate improved ambulatory care. It is unknown though what features it should incorporate to make it acceptable to persons from this particularly vulnerable target population. It also needs to be National Health Service (NHS) feasible. This project seeks to identify the optimal ACP configuration.

**Methods and analysis:**

Mixed-methods project comprising three-linked stages. In Stage 1, NHS bodies will be surveyed on ACPs they are considering and semi-structured interviews with PWE and their carers will explore attributes of care important to them and their concerns and expectations regarding ACPs. In Stage 2, Discrete Choice Experiments (DCE) will be completed with PWE and carers to identify the relative importance placed on different care attributes under common seizure scenarios and the trade-offs people are willing to make. The uptake of different ACP configurations will be estimated. In Stage 3, two Knowledge Exchange workshops using a nominal group technique will be run. NHS managers, health professionals, commissioners and patient and carer representatives will discuss DCE results and form a consensus on which ACP configuration best meets users’ needs and is NHS feasible.

**Ethics and dissemination:**

Ethical approval: NRES Committee (19/WM/0012) and King’s College London ethics Committee (LRS-18/19-10353). Primary output will be identification of optimal ACP configuration which should be prioritised for implementation and evaluation. A pro-active dissemination strategy will make those considering developing or supporting an epilepsy ACP aware of the project and opportunities to take part in it. It will also ensure they are informed of its findings.

**Project registration number:**

Researchregistry4723.

Strengths and limitations of this studyProject seeks to identify the optimal configuration of an ‘Alternative Care Pathway’ for epilepsy which could minimise clinically unnecessary and/or avoidable unplanned health service use and facilitate improved outcomes.The novel co-production approach employed—which will involve stakeholders at each project stage and use Discrete Choice Experiments (DCE)—will allow service users to inform service design in a scientifically robust, non-tokenistic way and could provide a template for service design more generally.Whilst most of the work packages will involve stakeholders from across England, patient and carers for the DCE are being recruited from one region. This might limit generalisability.The ACP configuration identified will be developed for use in the NHS and so may not be immediately applicable to other health systems. It will also require evaluation via a subsequent project.The project’s success will depend, in part, on service users from what is a particularly vulnerable population agreeing to participate and representative samples being generated.

## Introduction

### Context and drive for health service innovations

The National Health Service (NHS), like other health systems, is being asked to make cost savings, while improving care experience, outcomes and reducing health inequalities.^1 2^ Emergency department (ED) visits and admissions for the ambulatory care sensitive condition epilepsy provide an opportunity where service innovations could help achieve such aims. We describe a mixed-methods project to maximise the likelihood of such innovations being beneficial to service users and society.

### Epilepsy and unplanned service use

With a prevalence of ~1%,^3^ epilepsy is the UK’s second most common serious neurological disorder. Annually, ≤20% of people with epilepsy (PWE) visit hospital ED.^4–6^ They report more anxiety, seizures and perceived epilepsy stigma than those in the wider epilepsy population and live in more deprived areas^7–12^; ~20% have an intellectual disability.^13 14^

The annual cost to the NHS of these visits in England alone is ~£70–90M.^15–17^ Costs are high because half of the visits result in hospital admission.^6 18–21^ An unusually high re-attendance rate also inflates cost^22 23^;≤60% of PWE re-attend ED within 12 months.^7^

Most PWE visiting ED do not attend with a life threatening or emergency presentation, (eg, status epilepticus, first seizure). Rather, projects like our National Audits of Seizure Management in Hospitals (NASH)^13 14^ show that most have known, rather than new epilepsy, and present with states not requiring ED’s full facilities. Leading presentations include someone who has experienced: (i) an uncomplicated seizure in line with their usual presentation; (ii) a seizure in public and cannot be ‘left at scene’; and (iii) a self-terminating seizure, different to their usual presentation.^20^

### Unmet needs of PWE visiting ED

While the acute episodes leading PWE to visit ED do not typically require emergency care, the visits can be expressions of the person having received suboptimal ambulatory care and unmet needs. NASH^19^, for instance, found that most (~65%) PWE visiting ED are not known to specialist epilepsy services and many were via their usual care provider, seemingly receiving outdated care. For instance, despite focal epilepsy being the most common epilepsy type, most likely to be refractory and often not best treated with the medication sodium valproate, NASH found it to be the most prescribed medication among ED attendees.

Coping with life in the context of epilepsy also requires an individual to accept their diagnosis and learn and adopt a range of self-management behaviours to prevent seizures and manage consequences. PWE visiting ED though and their significant others appear to have less knowledge about epilepsy and its management, including seizure first aid.^7 24–26^ They might therefore benefit from enhanced self-management support, like that provided by epilepsy nurses. The reason that knowledge might be low in ED attendees is because there remains no routine course that all PWE can go on to learn about epilepsy (as there are for some conditions). People who have lower education levels appear to fare worst from this situation with them having been found to have the least epilepsy knowledge.^27 28^

That some PWE in the UK are receiving suboptimal care is well known, with there being longstanding challenges in ensuring that the PWE most in need of specialist care receive it. While trial evidence indicates ~70% of PWE can become seizure free, some evidence indicates only ~50% of PWE in the UK currently are,^29^ with PWE in socially deprived areas faring the worst.^30^ Factors contributing to the challenge are that the UK has a comparatively small specialist workforce^31^ and that there is no national, incentivised system to identify those within the epilepsy population that might need stepped-up care. To further complicate matters, General Practitioners (GPs), who care for most PWE, have expressed low confidence in managing the condition.

ED visits by PWE can be considered opportunities to intervene. Unfortunately, under current arrangements, going to ED does not typically lead to PWE receiving ambulatory care improvements. Bodies, such as The National Institute for Health and Care Excellence (NICE)^2^, recommend that when seizures are not controlled, a patient should be referred to specialist services (within 4 weeks) since this may improve outcomes, including rendering some seizure free.^32 33^ Most (80%) PWE visiting ED are though not seen by a specialist during their attendance, their usual care providers may not be informed of the attendance^13^ and most (60%) are not referred to a specialist for follow-up.

PWE living in the most deprived areas, as well as the elderly, are among the least likely to be referred on from ED.^34^ The low referral rate may be due to some clinicians holding an incorrect nihilistic view that intractability is inevitable if seizure control is not obtained within a few years of therapy onset. Assumptions about the willingness of certain patient groups to attend clinics may also be being made.^35 36^

### An ‘Alternative Care Pathway’

NHS policies^1 2 37^ and publicity given to NASH’s findings^15 38^ created momentum to reduce visits for seizures and enhance patient outcomes. NICE^39^ found no evidence on how to do this. However, one idea gaining traction is for ambulance services to assume a greater role.^40^ Most (~90%) people visiting ED for seizures have been transported there by an emergency ambulance.^13 14 21^

Data from some regional ambulance services on conveyance rates for seizures has been published. It indicates ambulance staff are recommending conveyance of nearly every person they attend for a suspected seizure to ED,^41–43^ despite most not demonstrating a clinical need (eg, seizures have self-terminated before ambulance arrival in ~90% of cases),^42^ One reason for this is paramedics lack access to alternatives.^44–46^ There is a vision therefore of what could help: ambulance service access to some form of ‘Alternative Care Pathway’ (ACP) whereby those seeking help for an epileptic seizures judged not to require ED are cared for within less costly, alternative environments.

The exact nature of the ACP is not clear. Different regions and services are considering different configurations and doing so in an uncoordinated way. ACPs being considered appear to include paramedics transporting patients’ home or to an urgent treatment centre rather than ED. Others involve paramedics leaving patients at scene with the offer of a telephone call from a nurse or general practitioner with a specialist interest in epilepsy within 24, 48 or 72 hours. A possible benefit of this latter configuration is health inequalities could be reduced by introducing a mechanism by which all PWE ‘in need’ are brought to specialists’ attention.

ACPs are not new^47^ and paramedics have not been obliged to transport patients to ED since ~1997. The ambitions of ACPs have though increased and there is significant support within the UK policy realm to expand the number of conditions covered by them as a means of managing demands on hospital services.^48–50^

ACPs within the ambulance have largely come about due to the ‘it seemed like a good idea at the time’ principle,^51^ rather than with reference to a behaviour change theory. Evidence on the utility of ACPs is though generally positive.^47 52–54^ In their review of potential revisions to the urgent and emergency care system, the Nuffield Trust identified greater ambulance/paramedic triage in the community as having the most the positive evidence of effectiveness.^40^ Paramedics appear willing and safely able to use ACPs when trained and for some ACPs there is evidence of cost-savings and greater patient satisfaction.^52 53^

In the case of epilepsy, qualitative research^44–46^ provides the beginnings of a theoretical basis for the use of an ACP in epilepsy with the mechanisms by which it could make a difference being that it may: increase awareness and likelihood that paramedics will consider non-conveyance and referral pathways as an option in appropriate cases; increase paramedics’ clinical knowledge of how to make appropriate non-conveyance decisions; increase paramedics’ knowledge of alternative care providers that are acceptable to service users; and increase paramedics’ confidence about making a non-conveyance decision and reducing anxiety about risk.

### Developing an ACP for epilepsy

An ACP for epilepsy holds potential. As a team of healthcare professionals, researchers and service user representatives with expertise in epilepsy and urgent care, our ultimate goal is therefore to evaluate the most promising ACP and use the evidence to transform service organisation nationally. However, we cannot currently do this because the way in which ACPs are being developed means it is not known which of the ACPs has the potential to be most effective and could be justified for selection.

Specifically, ACPs are being developed largely ‘top-down’, with the patient voice being absent. The nature and content of ACPs may not therefore align with what patients/carers would consider to meet their needs. Evidence suggests decisions to access healthcare services can be informed by how a patient/carer perceives their situation^55–57^ and there can be a mismatch between patients/carers and health professionals’ views, including of what constitutes an ‘emergency’.^58–61^ The upshot is the acceptability—a fundamental criterion an intervention needs to satisfy to be positioned to achieve its intended outcome^51^—of the different ACPs to patients and carers is unknown.

To date, only one epilepsy ACP has been reported on.^62^ Despite the evaluation revealing positive outcomes, less than 10% of eligible PWE attended to by paramedics were put onto the ACP. The reasons for this low uptake rate were not explored. A possible explanation is that the ACP was not acceptable to PWE.

It has been assumed the target population *does not* want to be conveyed to ED and will readily accept an ACP. It may not be that straightforward. Some PWE certainly express dissatisfaction with being taken to ED.^63^ Others though express a need for immediate access to urgent care; with some PWE and their family and friends (to whom care decisions are often delegated to when the patient is unconscious or lacks capacity) being fearful of seizures, including the possibility of brain damage.^25 26^

## Current project

This 28 month project seeks to identify the ACP that should be prioritised for testing/implementation. It seeks to shape the change that results from the identified momentum so the likelihood of patients and the NHS benefiting are maximised and finite health resources used in an informed, rational way. It will bring patients/carers from the target population, healthcare professionals and commissioners together to identify which ACP configuration best encapsulates the features important to patients and carers *and* is feasible within the NHS context. The focus will be on the care of adults with epilepsy, rather than children/young people, since discussion to date relating to the use of ACPs and ED care has largely focused on the former (eg,.^19 62^). As per NICE guidelines for epilepsy,^39^ adults are defined as those aged 18 years and older.

The project has three linked stages and will use survey techniques, qualitative methods, consensus meetings and Discrete Choice Experiments (DCEs) to achieve its aims (figure 1).^64 65^ DCEs are an attribute-based survey methodology, underpinned by the theory that any ‘good’ (including a health service) can be described by its constituent characteristics (attributes), and that the extent to which an individual prefers a ‘good’ depends on the levels these attributes take.^66^ We considered DCEs to provide an efficient, scientifically defensible, and non-tokenistic way of bringing the patient voice into ACP design since they allow a person’s stated preferences and priorities to be elicited by presenting them with a hypothetical scenario (eg, having a seizure at home) and asking them to choose which of two (or more) care options described by a series of attributes they prefer. The process is then repeated with alternative care choices being presented. By varying attribute levels and observing how participants change responses, the importance of attributes and the extent to which they drive preference can be inferred.

**Figure 1 F1:**
[figure not shown]
Research project process diagram. ACP/s, alternative care pathway/s; DCEs, Discrete Choice Experiments; EDS, Emergency Departments; GP, General Practitioner; HRA, health research authority; NHS, National Health Service; PICs, Participant Identification Centres; PWE, People with Epilepsy.

### Aims

Systematically identify ACPs being considered by the NHS for epilepsy and describe extent to which service users have been involved in their design (Stage 1a).Understand patient and carers’ decision-making processes for seeking or not seeking ED care, and their concerns and expectations regarding ACPs (Stage 1b).Identify the attributes of post-seizure emergency care that PWE and their carers consider important and identify if this differs by the context in which the seizure occurs (Stage 1b).Determine patient and carer preferences for post-seizure emergency care using DCEs and identify any subgroup differences (Stage 2b).Estimate uptake of different ACPs configurations by patients and subgroup differences (Stage 2b).Hold expert workshops to develop an optimal ACP following seizures, to be prioritised for implementation and evaluation via a subsequent project (Stage 3).

## Methods and analysis

This project will use qualitative and quantitative methods (figure 1). According to Greene *et al*’s^67^ conceptual framework, the purpose of using a mixed methods approach is ‘development’ (seeking to use the results from one method to help develop or inform the other method, where development is broadly construed to include sampling and implementation, as well as measurement decisions; Stages 1–2b) and ‘expansion’ (seeking to extend the breadth and range of inquiry by using different methods for different inquiry components; Stages 2b and 3).

Data collection and analysis for Stages 1a and 1b will be completed concurrently and independent from one another. From Stage 1 c onwards, the design will be sequential and dependent. During Stage 2a, the findings from the earlier stages will be integrated to develop the DCE. Following completion of analysis for Stage 3, findings from all the stages will be integrated in a narrative form when interpreting and reporting on the project’s findings. Particular attention will be given to how the findings from Stage 3 converge and diverge from the qualitative and quantitative findings from the earlier stages.

### Stage 1

#### Stage 1a: pathway survey

##### Purpose

Systematically identify ACPs being considered. Will allow ACPs presented within DCEs to include main ones being considered.

##### Design

Cross-sectional survey of NHS service providers asking respondents whether their service has considered (or implemented) any changes to the management of those with epilepsy/suspected seizures to minimise clinically unnecessary/avoidable ED visits. Respondents will report how change is anticipated to minimise visits and whether service users informed change.

The survey will take ~10 min, be piloted and completed online. Survey respondents will be able to indicate if they want to be informed of subsequent project parts.

##### Recruitment

Invitations to participate, followed by two reminders, will be sent to clinical leads/directors of England’s regional ambulance trusts (n=11), regional neuroscience (~n=25)^68^ and neurology centres (~n=16),^69 70^ and a random sample of 25% of its ‘Type 1’ EDs^71^ (n=35), stratified by geographical area and size (attendances).

##### Analysis

Characteristics of responding and non-responding organisations will be compared. To determine the types of ACPs being considered and proportion of organisations considering each, a subset of surveys will be selected. A qualitative researcher, supported by the wider team, will read these to identify recurrent ACP types and collate them into a thematic coding framework. The framework will be applied to the full data set and modified to ensure all ACPs types are captured.

#### Stage 1b: qualitative interviews

##### Purpose

Understand patient and carer decision-making, the important attributes of post-seizure care, and concerns and expectations regarding ACPs. Will permit attribute development to adhere to good practice.^72 73^

##### Design

Face-to-face semi-structured interviews will be conducted with PWE, and where possible an informal carer, and shaped by a piloted topic guide (online supplementary file 1).

10.1136/bmjopen-2019-031696.supp1Supplementary data

Participants will be asked for contextual information about their epilepsy and ED visits. The researcher will explore patients and carers confidence in managing seizures and the decision to call the ambulance services. The influences on ambulance use and ED use when seizures occur in public places will also be examined. Evaluative information will then be sought regarding positive and negative perceptions of the ambulance service and casualty as well as any ACPs experienced. Potential attributes will be identified by describing two known ACPs (ie, urgent care centres and being taken home) and asking participants for their expectations and concerns.

To help reduce the number of care attributes and improve face validity, participants will rank what they consider to be the five most important care attributes. Interviewer will help recall those mentioned and write them onto show cards.

To promote consistency, interviews will be conducted by one experienced qualitative researcher ([name]). [name] (PhD), is a university-based qualitative researcher with an interest in health services research but no specialist knowledge of, or involvement in, the ambulance or emergency medical services. Before agreeing to take part, participants will be given a participant information sheet detailing the research. Written informed consent will be obtained (by [name]) before the interviews. No non-participants will be present during the interviews. Interviews will take place at a time and place convenient to the participant. It is anticipated they will last 60–90 min.

To promote transparency, meticulous records of the interviews will be kept, interviews audio-taped, transcribed verbatim^74^ and reported according to Consolidated criteria for Reporting Qualitative research.^75^

##### Recruitment

Aim is to capture a comprehensive range of perspectives, and sample size will be determined by data saturation. We anticipate^72 76^ recruiting a purposive sample of ~30 PWE, with or without an informal carer. Table 1 lists the inclusion and exclusion criteria.

**Table 1 T1:** Participant inclusion and exclusion criteria

Study part	Inclusion criteria	Exclusion criteria
**Stage 1b—Qualitative interviews**		
	Established diagnosis of epilepsy, or an informal carer for someone with epilepsy Age≥18 years (no upper age limit) Have visited ED in the past 12 months for epilepsy (as reported by the patient)* Able to provide informed consent and communicate in English	Severe current psychiatric disorders (eg, acute psychosis) Life-threatening medical illness
**Stage 2—Discrete choice experiments**		
Group 1 Patients	Clinically confirmed diagnosis of epilepsy (for any duration) Any epilepsy syndrome and any types of focal or generalised seizures Currently being prescribed antiepileptic medication Age≥18 years (no upper age limit) Have visited ED in the past 12 months for epilepsy Able to provide informed consent and independently complete a questionnaire in English Lives in the North West of England	Severe current psychiatric disorders (eg, acute psychosis) Life-threatening medical illness Resides within a care or nursing home or of no fixed abode
Carers	A significant other to a person with epilepsy (eg, family member, friend) who the patient identifies as providing informal support or self-identifies themselves if the patient has a substantial intellectual disability The person with epilepsy they care for has visited ED in the past 12 months Age≥16 years (no upper age limit) Able to provide informed consent and independently complete a questionnaire in English Lives in the North West of England	Severe current psychiatric disorders (eg, acute psychosis) Life-threatening medical illness
Group 2 Patients	Clinically confirmed diagnosis of epilepsy (for any duration) Any epilepsy syndrome and any types of focal or generalised seizures Currently being prescribed antiepileptic medication Age≥18 years (no upper age limit) Has *not* visited ED in the past 12 months, but has had a seizure with loss of awareness in this period Able to provide informed consent and independently complete a questionnaire in English Lives in the North West of England	Severe current psychiatric disorders (eg, acute psychosis) Life-threatening medical illness Resides within a care or nursing home or has no fixed abode
Carers	A significant other to a person with epilepsy (eg, family member, friend) who the patient identifies as providing informal support or self-identifies themselves if the patient has a substantial intellectual disability The person with epilepsy they care for has *not* visited ED in the past 12 months, but had a seizure with loss of awareness in this period Age≥16 years (no upper age limit) Able to provide informed consent and independently complete a questionnaire in English Lives in the North West of England	Severe current psychiatric disorders (eg, acute psychosis Life-threatening medical illness

*Should recruitment prove slower than anticipated, the recruitment criteria will be relaxed to allow people who have had ED or ambulance contact within the last 2 years.

ED, emergency department.

Eligible PWE will be identified by two means. First, persons with uncontrolled epilepsy who participated in a recent National Institute for Health Research (NIHR) funded ‘Self-Management Education for adults with Epilepsy’ trial in the South-East of England and expressed interest in future projects will sent notification of the study.^77^ Second, adverts will be circulated to persons affiliated with epilepsy user groups, including Epilepsy Action. Persons interested in taking part will be asked to contact the research team. To identify carer participants, patients will be asked to choose a significant other/informal carer to take part. Participants will receive a £20 shopping voucher.

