##### Recruitment

General Practices in North-West England will identify potential patient participants by searching their epilepsy registers.^86^ Practices will be recruited with the help of the NIHR Clinical Research Network North West Coast. Practices will send ostensibly eligible patients invitation packs via ‘Docmail’ and a repeat invite 2 weeks later to those not responding. Patients not wishing to participate will be encouraged to notify the team and detail their reasons. Eligibility criteria are in table 1.

A definitive sample size calculation depends on the finalised design of the DCE.^87^ To permit decisions regarding recruitment to be made in the meantime we anticipated the design and calculated the required sample size by using Orme’s^88^ formula. Full details are provided in box 1. This indicated 348 PWE (or associated informal carers) would be required, comprising data 174 patients (or associated carers) who have visited ED in the prior 12 months and 174 patients (or associated carers) who have not.

Box 1Sample size calculation for discrete choice experimentsFormula used and factors considered in estimating likely sample size requiredOrme’s formulae: (*n***t***a*)/ *c* must be ≥500, where *n* is number of respondents, *t* number of tasks, *a* number of alternatives per task, and *c* number of analysis cells (for main effects, the largest number of levels for any one attribute).Anticipated discrete choice experiments (DCEs) to involve participants being asked to make (*t*) nine separate choices between (*a*) two care packages and (*c*) three would be maximum attribute levels. Thus, Orme’s formula indicated complete data from n=84 needed.Intend to complete DCEs for three different seizure scenarios, but participants would only complete two, therefore 126 participants required.To allow for variation in the finalised number of choice tasks and levels we increased this to 150 and further inflated it to 174 to accommodate for ~15% of missing data experienced by prior epilepsy DCEs.As an objective was to describe and compare care preferences of two subgroups (patients (and associated carers) who have visited an ED in the prior 12 months versus patients (and associated carers) who have had a seizure in the prior 12 months, but have not visited an ED), 174 patients (and associated carers) who have visited ED in the prior 12 months and 174 patients (and associated carers) who have not, will need to be recruited.Total sample size, thus n=348.

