Based on responses to prior health DCEs^89^ and studies with PWE,^16 24^ we anticipate 30%–60% of those invited will agree to participate. An average English GP practice^90^ will have 24 PWE aged ≥18 on their register who have experienced ≥1 seizure in the prior 12 months,^9^ with 10 having visited an ED during that period.^12–14^ Governed by the need to recruit a subgroup of 174 PWE who have visited ED in the prior 12 months, 29–58 general practices will be required.

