##### Analysis

Data for the different seizure vignettes will be analysed separately using an error components logit model that allows for a panel of responses from the same respondent. This will determine the importance of the different care attributes for preference and direction of effect (as indicated by the significance of the coefficients and their size). Comparison between vignettes will depend on attribute and level specification of each experiment. Analyses will be completed with and without respondents failing a ‘rationality’ test.

Marginal rates of substitution (the rate at which respondents are willing to give up a unit change in one attribute in exchange for a unit change in another while maintaining the same level of utility) will be calculated using each quantitative attribute as the value attribute with bootstrapped confidence intervals (1000 reps).

Preference heterogeneity will be assessed by estimating a mixed logit model, which will include random parameters for the attributes, and interactions between attributes and respondent characteristics.^91^ A-priori characteristics of interest are: (1) emergency care for epilepsy in the past 12 months (paramedic and/or ED visit), (2) social deprivation (with participants grouped according to how socially deprived the area is within which they live); (3) whether or not they have seen an epilepsy specialist within the prior 12 months (which they should have according to NICE guidelines^88^ given they will all have uncontrolled epilepsy); and (4) whether they or the person they know in the case of carers, self-reports an intellectual disability.

‘Utility scores’ for different ACP configurations and significantly different populations will be calculated and ranked accordingly. Their uptake under different seizure scenarios will be estimated.

All analyses will be conducted in STATA V.11.

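### The non-ED group must have had a seizure with loss of awareness in Table 1 but only a seizure in Box 1 and the practice count; Group 1 has no awareness condition, so the ED-visit comparison may partly reflect eligibility

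*Protocol article*

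**What the plan says.** The Stage 2 rows of Table 1 define the two comparison groups.

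- **Group 2 patients** have had no ED visit in the past 12 months, "but has had a seizure with loss of awareness in this period". The Group 2 carer row sets the same condition for the person cared for: "but had a seizure with loss of awareness in this period".
- **Group 1 patients** qualify through an ED visit: "Have visited ED in the past 12 months for epilepsy". No awareness condition is attached. The Group 1 carer row reads "The person with epilepsy they care for has visited ED in the past 12 months", without saying that the visit was for epilepsy.
- **Both patient groups** admit "Any epilepsy syndrome and any types of focal or generalised seizures".

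Elsewhere the non-ED group is described more broadly. Box 1 has people "who have had a seizure in the prior 12 months, but have not visited an ED". The Stage 2b Design section speaks of people with uncontrolled epilepsy and no ED visit. The Stage 2b Recruitment section builds the practice count from 24 adults per practice "on their register who have experienced ≥1 seizure in the prior 12 months", of whom 10 visited an ED.

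The Stage 2b Analysis section names four a-priori respondent characteristics: emergency care, deprivation, specialist contact and intellectual disability. Seizure type or awareness is not among them. In explaining the specialist-contact item it says of the respondents, "given they will all have uncontrolled epilepsy".

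**The concern.** Describing and comparing preferences by ED use is the reason Box 1 gives for recruiting two groups of 174 rather than one. As Table 1 stands, the groups differ by rule in one respect besides ED use: people whose seizures are all without loss of awareness may be in Group 1 and are barred from Group 2.

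Awareness could plausibly bear on the preferences being measured. The Introduction notes that care decisions often pass to family and friends when the patient is unconscious or lacks capacity. A difference in attribute coefficients between the groups could then come partly from who was eligible. No listed characteristic would show this.

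There is also a recruitment question. The statement that ED visitors govern the number of practices compares them, implicitly, with a non-visitor pool counted on any seizure. Table 1 admits only part of that pool.

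**Working it through.** **1. The plan's own figures.** Inputs from Box 1: 9 tasks, 2 alternatives, at most 3 levels, threshold 500.

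- Orme's rule: 500 × 3 / (9 × 2) = 83.3, so 84.
- Two of three scenarios per respondent: 84 × 3/2 = 126.
- The plan raises this to 150, then to 174 for about 15% missing data. The two usual inflations give 150 × 1.15 = 172.5 (173) and 150 / 0.85 = 176.5 (177), so 174 is consistent.
- Two subgroups: 2 × 174 = 348.
- Practices, from 10 ED visitors per practice and 30%–60% participation: 174 / (10 × 0.60) = 29 and 174 / (10 × 0.30) = 58.

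All figures reproduce. None uses the seizure definition of Group 2, so the mismatch alters none of them directly.

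**2. When Group 1 really governs the practice count.** The non-visitors per practice are 24 − 10 = 14, inferred by subtraction and counted on any seizure. Let s be the share of these who had a seizure with loss of awareness. The article gives no value for s, so every value below is an assumption.

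- Group 2 practices needed = 174 / (14 × s × participation).
- Group 1 governs only while 14s ≥ 10, that is s ≥ 10/14 = 71%.

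| Assumed s | Eligible non-visitors per practice | Practices at 60% to 30% participation | Group 2 recruits from 29–58 practices |
|---|---|---|---|
| 100% | 14.0 | 21–42 | 244 |
| 80% | 11.2 | 26–52 | 195 |
| 70% | 9.8 | 30–60 | 171 |
| 60% | 8.4 | 35–70 | 146 |
| 50% | 7.0 | 42–83 | 122 |

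The last column is 29 × 14s × 0.60, which equals 58 × 14s × 0.30. At s = 50% it is 29 × 7 × 0.60 = 121.8, against the 174 wanted. Like the plan's own calculation, the table counts patients only, although either a patient or an associated carer may count towards each 174.

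**3. The eligibility asymmetry.** Reading the Table 1 rows together:

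| 12-month history | Group 1 | Group 2 |
|---|---|---|
| ED visit for epilepsy, only aware seizures | admitted | – |
| ED visit for epilepsy, seizure with loss of awareness | admitted | – |
| No ED visit, only aware seizures | – | excluded |
| No ED visit, seizure with loss of awareness | – | admitted |

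The effect on the contrast would depend on the share of Group 1 with only aware seizures and on how far their preferences differ. The article gives neither, so no size or direction can be calculated.

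**The case against.** The strongest defence is that Table 1 governs. The Recruitment section refers the reader to it for eligibility, so Box 1 and the practice count can be read as shorthand. That stands as an account of which definition applies. It leaves the non-visitor pool counted on a broader basis than the one that will be recruited.

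A second defence is that requiring loss of awareness may be deliberate. The Stage 2b Design section seeks people at risk of an ED visit, and the restriction could make non-visitors more like attenders. This is plausible, and it is one reason the direction of any effect is unknown.

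Three stronger readings are tempting and should not be drawn.

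- **That Group 1 need not have had a seizure at all.** For patients, an ED visit for epilepsy largely implies one, and the practice count places the 10 visitors within the 24 with a seizure. What is absent is the awareness condition.
- **That the comparison is confounded by seizure type.** The documents show unequal eligibility, not an imbalance between the groups. The stated aim is to describe and compare, not to attribute differences to ED use. The Introduction already reports that attenders differ in anxiety, seizures, stigma and deprivation, so equalising awareness would not make the contrast causal.
- **That 29–58 practices is wrong.** It follows exactly from the 10 visitors per practice and fails only if s is below 71%. At an assumed 80%, Group 1 still governs.

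It is also fair to say that further covariates and sensitivity analyses may be left to an analysis plan, and that respondents will report on their epilepsy, so an adjustment is feasible. That keeps the remedy small. It does not remove the inconsistency in the published definitions.

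**Conclusion.** The point holds as an inconsistency of definition with a possible effect on interpretation. Group 2 is narrower in Table 1 than in Box 1, in the Stage 2b Design section and in the pool behind the practice count, and only Group 2 carries the awareness condition. The ED-visit comparison may therefore partly reflect eligibility, by an amount and in a direction that the documents do not allow one to state.

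The sample sizes of 84, 126, 174 and 348 stand. The practice range of 29–58 stands on an unstated condition, s ≥ 71%, which rests on the plan's 24 and 10 per practice and on equal participation in both groups.

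The statement that all respondents have uncontrolled epilepsy goes further than the Group 1 criteria ensure. This is clearest in the carer row, where the ED visit need not have been for epilepsy.

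**What to change.** - Leave Group 1 eligibility as it is. Imposing the awareness condition there would exclude real ED users from a sample meant to represent them.
- Use the Table 1 definition of Group 2 in Box 1, the Stage 2b Design section and the practice count.
- Record in both groups whether a seizure with loss of awareness occurred in the past 12 months. For carers, record it for the person they support.
- Keep the full-sample ED-visit contrast, and add a sensitivity contrast restricted to respondents with such a seizure, or adjusted for it.
- State beside the range of 29–58 that it suffices only if at least 71% of the 14 non-visitors per practice meet the Table 1 criterion, and give the share assumed.
- Qualify the statement about uncontrolled epilepsy, and reconcile the Group 1 carer row with the patient row on whether the ED visit was for epilepsy.

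The cost is wording in a few places, one questionnaire item if the epilepsy questions do not already cover it, and one extra analysis. The restricted contrast will have a somewhat smaller sample, and the stated practice range may become less favourable.
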